## Abstract

**Background:**

In recent years, the prevalence of non-communicable diseases (NCDs) has escalated. Evidence suggests that there are strong associations between nutrition in early life and the risk of disease in adulthood. This manuscript describes the study protocol of the First United Arab Emirates National Representative Birth Cohort Study (UAE-BCS), with the objective of investigating nutrition and lifestyle factors in the first 1,000 days of life. The main aims of the study are (1) to address critical issues relating to mother and child nutrition and their effect on growth and development, (2) to profile maternal nutrition, child growth, health, and development outcomes in early life, and (3) to study the associations between these factors among the Emirati population in the UAE.

**Methods/Design:**

In this study, a multidisciplinary team of researchers was established including credible researchers from the UAE, Lebanon, Australia, and the United Kingdom to launch the First United Arab Emirates 3-year birth cohort study. We aim to recruit 260 pregnant Emirati women within their first trimester, which is defined by the study as from 8 to 12 weeks pregnant, from obstetrics and gynecology clinics in the UAE. Participants will be recruited via face-to-face interviews and will receive a total of 11 visits with 1 visit in each trimester of pregnancy and 8 visits after delivery. Maternal data collection includes, socio-demographic and lifestyle factors, dietary intake, anthropometric measurements, physical activity, maternal psychological state, and blood samples for biochemical analysis. Post-partum, visits will take place when the child is 0.5, 4, 6, 9, 12, 18, and 24 months old, with data collection including infant anthropometric measurements, young child feeding practices, dietary intake, supplement use and the eating environment at home, as well as all maternal data collection described above, apart from blood samples. Additional data collection for the child includes early child developmental assessments taking place at three timepoints: (1) within 2 weeks of birth, (2) at 10–14 months and (3) at 22–26 months of age. Early child developmental assessments for the infant include vision, hearing, cognition, motor skills, social-emotional reactivity, neurodevelopmental, and sleep assessments.

**Discussion:**

The United Arab Emirates Birth Cohort study protocol provides a standardized model of data collection methods for collaboration among the multisectoral teams within the United Arab Emirates to enrich the quality and research efficiency in early nutrition, thereby enhancing the health of mothers, infants, and children.

## Introduction

Globally the impact of NCDs continues to grow, and they have become the leading cause of mortality, with type T2DM being the fourth most deadly NCD (1, 2). During the past three decades, the global prevalence of T2DM has doubled and now presents a significant public health challenge in almost every country. In 2019, the International Diabetes Federation (IDF) estimated the global prevalence of T2DM to be 9.3%; however, it is thought that around 50.1% of people with diabetes remain undiagnosed. Additionally, the prevalence is estimated rise to 10.2% by 2030 resulting in 115 million new cases between 2019 and 2030. The Middle East and North Africa (MENA) region is ranked the highest region for the prevalence of diabetes accounting for 54.9 million of the global prevalence (3), the United Arab Emirates (UAE) part of the three countries with the highest prevalence of diabetes in the MENA region with 12.3% of the population living with the disease (4, 5). In the UAE, four NCDs are responsible for 65% of all deaths; cardiovascular disease, cancer, diabetes, and chronic respiratory disease (6). A 2010 study in the UAE showed the prevalence of prediabetes to be 31% and undiagnosed diabetes mellitus 14.6%. Another significant health issue is metabolic syndrome (MetS), the concurrent existence of prediabetes, dyslipidemia, elevated blood pressure, and obesity (7).

It is widely acknowledged that most NCDs identified in adults have their origins in early life. The theory of the developmental origins of adult diseases, commonly known as the Barker hypothesis, associates nutrition during pregnancy, and risk of chronic disease in later life (8). Accumulating evidence shows that a balanced and varied diet plus a healthy lifestyle in the months leading up to conception, throughout pregnancy, during infancy, and to the second birthday, collectively known as the first 1,000 days of life, are influential to health and risk of disease later in life. For instance, full-term infants who are small-for-gestational age have an increased risk of cardiovascular disease (CVD) and T2DM in adulthood, and this is a known consequence of fetal undernutrition (9). Studies on the relationships of nutritional imbalances in early life with birth outcomes, growth patterns, and early determinants of NCDs, have revealed direct associations between limited maternal weight gain during pregnancy and both impaired fetal growth, and low birth weight (10). Also, excess maternal weight gain correlates with high birth weight and fetal growth (large-for-gestational age) (11, 12), as well as adverse cardiometabolic profiles in the offspring (13). In addition to maternal weight gain, maternal diet composition and micronutrient status during pregnancy seem to be associated with birth outcomes and child health status.

The first 1,000 days of life are a vital period that play a crucial role in the development of the immune, endocrine, metabolic, motor, and other developmental pathways. Maternal nutrition and lifestyle choices in preconception and during pregnancy have significant influences on the health, growth, and development of the fetus. Research shows that a maternal diet low in protein is connected to changes in the structure of the liver of the fetus and low birth weight (14), while a diet rich in fat effects adipocyte metabolism, fetal growth, and fat mass in the offspring (15, 16). Maternal anemia and iron, folate, or vitamin B12 deficiency during pregnancy is associated with an increased risk of fetal growth restriction, premature birth, and low birth weight (17–19). The effect of maternal nutrition on the cognitive capability and neurodevelopment of offspring is well established, particularly in the context of micronutrient deficiencies. Vitamin B12 deficiency is associated with spina bifida and infant insulin resistance (20), and maternal iodine deficiency with hypothyroidism. Prenatal maternal iron deficiency is associated with decreased myelination, disturbance in monoamine neurotransmitter synthesis and hippocampal energy metabolism in offspring (21), and there is evidence of an association between increased consumption of essential long-chain omega -3 fatty acids during pregnancy and better infant performance in development assessments, verifying the link between prenatal and postnatal diet to specific aspects of the brain development (22). The effect of prenatal maternal nutrition on neurodevelopment outcomes in children is not exerted solely through the effect of maternal nutrition on fetal growth and birth outcomes. It persists into the postnatal period, by impacting the quality and quantity of breast milk, maternal mood, and infant feeding practices.

Maternal and infant nutrition may influence the risk of later disease due to its critical associations with immunological development of the fetus and young infant (23). Adequate nutrition is necessary both for establishment of the immune system, normal organogenesis and development, and development of an adequate immune response. Undernutrition during early childhood exerts a concomitant effect on cognitive and developmental milestones through mid- and late- childhood and into adolescence. Studies consistently identify associations between stunting at ages 2 and 3 years with later cognitive deficit, as well as school achievement, even after controlling for socio-demographic confounders (24).

Global estimates of stunting and wasting in children under the age of five for 2018 were reported to be 21.9% (149 million) and 7.3% (49 million), respectively, and obesity in children of the same age group was reported to be 5.9% (40 million). The MENA region has the second highest rate of under 5 years overweight children, with an increase from 8.9% in 2,000 to 11.2% in 2018 (25). According to the UNICEF, in 2020 the UAE mortality rate for children under five was 6.6 per 1,000 live births, for infants was 5.6 per 1,000 live births, and neonatal mortality rate was 3.6 per 1,000 births (26). The percentage of overweight school and adolescent children (5–9 years) was estimated to be 37% in 2016 (27). However, there are no records for malnutrition, stunting and wasting of children in the country.

In some research from the UAE, the overall prevalence of global development delay and pervasive development disorder among 3-year old children was reported to be 2.44% and 29 in 10,000 for severe development delay/disorder with a prevalence of 8.4% and 58 in 10,000 for mild to moderate delay/disorder (28). Currently, there are no reports of the neurodevelopmental abilities of young children during the first 1,000 days of life from the UAE. These indicators are considered key public health factors, which contribute independently to mortality and burden of disease.

### Objectives

The objective of the first UAE -BCS is to recruit 260 pregnant Emirati women and to profile the maternal nutrition, child growth and developmental outcomes during the first 1,000 days of life in the UAE. This 3-year, prospective observational study seeks to address critical issues relating to mother and child nutrition and its effect on growth and development. Specifically, given that maternal and paternal health has a transgenerational impact on the development and health of offspring, this cohort study aims to profile maternal nutrition, child growth and development outcomes, and to study the association between these in the UAE. Accordingly, the establishment of a body of evidence through this cohort study is of paramount importance to inform future strategies regarding optimal dietary intake and consequent nutrition-related health of women in childbearing age and their offspring. The objectives of this cohort study involve:

-Characterization of the *in utero* environment through assessment of antenatal maternal and paternal factors such as, weight gain, abnormal gestational glucose tolerance, pregnancy-induced hypertension, preterm births, and new-born small- and large—for gestational age birth weight on new-born body composition, birth outcomes, and growth patterns.-Studying the association between early feeding practices including breastfeeding, weaning, and complementary feeding patterns, as well as postnatal growth and adiposity for the first 1,000 days of life.-Studying the association between specific maternal micronutrient status (vitamin B12, vitamin A, vitamin D, hemoglobin, ferritin, folate, lead, and zinc) and gestational weight gain with offspring body composition, birth outcomes and growth patterns.-Determining the impact social and environmental conditions, including family structure, socioeconomic status, health behaviors (i.e., dietary intake and physical activity), and maternal psychological stress factors on the development of adiposity of the growing offspring in the first 1,000 days of life.-Developing and validating the Neonatal Neurodevelopment Assessment (Neo-NDA) for the measurement of neurological status and maturity in new-borns, which will ultimately serve clinical and academic research purposes.

## Methods and Analysis

### Ethical Approval

The UAE-BCS protocol was approved by the United Arab Emirates University Human Research Ethics Committee, (ref. ERH-2020-61442020-12). Additional approval was granted from the Ministry of Health and Prevention (Approval Reference No: MOHAP/DXB-REC/NDD/No.162/2020.) and the Department of Health Abu Dhabi (ref: DOH/CVDC/2021/510). This study is registered at clinicaltrials.gov (NCT04928898).

### Study Design

The UAE-BCS is a prospective, observational, population-based 3-year cohort study of expecting Emirati females and their children living and attending obstetrics and gynecology (OB-GYN) clinics in the UAE. In 2021, the UAE population was reported to be 10 million, however, the expatriates constitute the majority of the population, and the Emirati population was estimated to account for almost 1 million of the entire population in 2010 (29, 30). The UAE has seven Emirates in which the Emirati population is reported to be a s follows; Emirate of Abu Dhabi was estimated to have 551,353 Emiratis in 2016; the Emirates of Dubai was estimated to have 233,430 in the same year, and most recently 271,050 in 2020; Ras Al Khaimah had 127, 000 Emiratis in 2015. However, data for Ajman, Umm Al Quwain and Fujairah estimated 42, 186, 17,482 and 64,860 Emiratis in 2010, respectively. Additionally, in all Emirates males account for most of the Emirati population in all Emirates with the exception of Umm Al Quwain in which 8, 811 of the 17, 482 were female in 2010 (31–34).

For this study, the UAE will be stratified into three geographic areas based on population density and socioeconomic factors: Abu Dhabi, Dubai, and the Northern Emirates. Approximately 40% of participants will be recruited from Kanad Hospital, Al Ain, Abu Dhabi; 30% of participants from facilities in Dubai, and 30% from clinics across the Northern Emirates.

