### Study Participants

The study aims to recruit a total of 260 pregnant Emirati females during their first trimester (8–12 weeks of gestation) through face-to-face recruitment at OB-GYN clinics in selected health care facilities across the Emirates of the UAE. The participants will be provided with both verbal and written information (Participant Information sheet) about the study aims, data collection activities, and duration of the study. Mothers will consent to the study on behalf of their children to be included in the study, by signing a form, after meeting the following inclusion and exclusion criteria.

Inclusion Criteria:

•Emirati Nationality•Within first trimester of pregnancy (between 8–12 weeks of gestation)•Singleton pregnancy•Absence of major illness preconception (Diabetes mellitus, hypertension, kidney disease, cancer, epilepsy, severe psychiatric illness, and other chronic diseases of infections such as autoimmune disorders, human immunodeficiency virus, and hepatitis).

Exclusion Criteria:

•Non-Emirati Nationality•Unconfirmed viable, intrauterine pregnancy at first obstetric ultrasound during first trimester•Twin or multiple gestation pregnancy and a history of multiple gestations•History of chronic illness (i.e., T2DM, hypertension, etc.)•Previously given birth to babies with malformation, intellectual disability, or inborn errors of metabolism.•Experience of a miscarriage before 28 weeks of gestation•Use of significant regular medications, including insulin, anti-hypertensive agents, psychotropic medications, anti-epileptic drugs, steroids, immune-suppressive agents, and chemotherapeutic agents.

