Frequencies and percentages will be used to describe categorical variables and mean, and standard deviations will be used to describe continuous variables. The chi-square test (χ2) or Fisher’ s exact test will be used to calculate the association between categorical variables. Independent *t*-tests and Mann-Whitney tests will be used to chart comparisons for normal and non-normal continuous variables, with normality of variables evaluated using the Kolmogorov-Smirnov and Shapiro-Wilk tests. Associations among the variables of the cohort study (i.e., maternal factors, birth outcomes, breastfeeding, complementary feeding, growth patterns, etc.) will be examined using simple linear and logistic regressions. The two main dependent variables in this study are related to birth outcomes and growth patterns of the child. Variables showing statistical significance in the univariate analysis will be included in the multivariate models as covariate factors in order to control for potentially confounding variables that have been used in the model. Parameter estimates and their respective 95% confidence intervals will be calculated for linear regression analyses, whilst for logistic regression analyses odds ratios and their respective 95% confidence intervals will be calculated. Tests for linearity (tolerance > 0.4) of the covariates included in the regression models will be performed. Normality of the residuals will be assessed using the histogram of standardized residuals and normal probability plot in all linear regression models. *P*-values less than 0.05 will be considered to indicate statistical significance.

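### The cohort is labelled nationally representative but is a regional quota sample from selected clinics, and the covariate rule does not secure the design stratum (region) in the models

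*Protocol article*

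**What the plan says.** The Abstract (Background) names the study the "First United Arab Emirates National Representative Birth Cohort Study (UAE-BCS". Under Study Design it is described in similar terms: "The UAE-BCS is a prospective, observational, population-based 3-year cohort study". The Discussion criticises earlier UAE studies for not being nationally representative.

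Study Design then gives the sampling scheme: "the UAE will be stratified into three geographic areas based on population density and socioeconomic factors: Abu Dhabi, Dubai, and the Northern Emirates". The allocation is "Approximately 40% of participants will be recruited from Kanad Hospital, Al Ain, Abu Dhabi; 30% of participants from facilities in Dubai". The remaining three in ten women are to come from Northern clinics. Study Participants describes "face-to-face recruitment at OB-GYN clinics in selected health care facilities across the Emirates of the UAE". The eligibility criteria exclude, among others, women with a chronic illness, women on significant regular medication and women with certain earlier pregnancy outcomes.

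Statistical Analysis and Sample Size Calculation plans plain description ("Frequencies and percentages will be used to describe categorical variables", with means and standard deviations for continuous variables), simple linear and logistic regressions, and multivariable models. Covariates for the latter are the variables that reach significance in univariate analysis. Neither region nor site is named.

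**The concern.** Two statements in the article do not fit the design it describes.

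**The label.** Profiling maternal nutrition and child growth in the Emirati population is a stated aim, and the Conclusion wants the results to inform national policy. A reader will take the profile estimates as national ones. They would come from a quota sample of women without chronic illness attending selected clinics, with the largest region covered by a single hospital.

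**The covariate rule.** The strata were drawn because the regions are taken to differ in density and socioeconomic factors, and the Objectives treat socioeconomic status as a determinant of child adiposity. Region is therefore a plausible common cause of maternal exposures and child outcomes. A stratum built into the design should be in the models by decision. Under the stated rule it is there only if it happens to reach P < 0.05.

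**Working it through.** **1. The plan's own sample size.** Inputs from the sample size section: r = 0.2, 80% power, 5% type I error (taken as two-sided). With Fisher's z:

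n = ((1.960 + 0.842) / atanh(0.2))² + 3 = (2.802 / 0.2027)² + 3 = 193.97, rounded up to 194.

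This matches the stated 194. The 35% increase gives 194 × 1.35 = 261.9, against the stated 260.

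**2. Quotas in women.** 0.40 × 260 = 104 from the one Al Ain hospital; 0.30 × 260 = 78 from Dubai; 78 from the North.

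**3. Quotas against the article's population counts (Study Design).** Abu Dhabi 551,353 (2016). Dubai 233,430 (2016) or 271,050 (2020). North, as listed: 127,000 + 42,186 + 17,482 + 64,860 = 251,528 (2015 and 2010). Seven emirates are mentioned but only six have a count. The seventh is assumed to fall in the Northern stratum and is varied from 0 to 300,000.

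| Dubai count | Seventh emirate (assumed) | Abu Dhabi | Dubai | North |
|---|---|---|---|---|
| 2016 | 0 | 53.2% | 22.5% | 24.3% |
| 2016 | 100,000 | 48.5% | 20.5% | 30.9% |
| 2016 | 300,000 | 41.3% | 17.5% | 41.3% |
| 2020 | 0 | 51.3% | 25.2% | 23.4% |
| 2020 | 100,000 | 47.0% | 23.1% | 29.9% |
| 2020 | 300,000 | 40.1% | 19.7% | 40.1% |
| **Quota** | | **40%** | **30%** | **30%** |

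Dubai is over-sampled in every row, from 30/25.2 = 1.2-fold to 30/17.5 = 1.7-fold. Abu Dhabi is under-sampled or, at best, about proportional. The North can go either way.

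**4. How reliably the screen admits region.** Region has 2 degrees of freedom. With N = 194, the F test at 5% has noncentrality λ = N·R²/(1 − R²), where R² is the share of outcome variance explained by region. The R² values are assumptions, because the article gives no regional data.

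| R² | λ | Probability that region passes |
|---|---|---|
| 0.02 | 3.96 | 41% |
| 0.03 | 6.00 | 58% |
| 0.05 | 10.21 | 82% |

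**5. What is lost when region is missed.** Suppose there is no association within regions, region explains the same R² of exposure and outcome, and the regional means line up perfectly. The induced correlation then equals R²: 0.02, 0.03 or 0.05. At n = 195 it is significant 5.9%, 7.0% or 10.7% of the time, against a nominal 5%. If region explains 13% of the exposure and 2–5% of the outcome, the induced r is √(0.13 × 0.02) to √(0.13 × 0.05), about 0.05 to 0.08.

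For a large regional effect, let the two 30% regions lie +0.5 and −0.5 SD from the third in both variables. The between-region variance is 2 × 0.3 × 0.25 = 0.15, so the induced r is 0.15/1.15 = 0.13, significant 44% of the time in an unadjusted analysis at n = 195. But region then explains 13% of outcome variance and passes the screen about 99.9% of the time, if it is screened.

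**6. Cost of forcing region in.** Two indicators give n = 190.97 + 3 + 2 = 195.97, rounded up to 196. With 194 analysed, power is Φ(0.2027 × √189 − 1.960) = 79.6%, against Φ(0.2027 × √191 − 1.960) = 80.0% without region.

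**The case against.** The case against has real weight on several points.

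- **Confounding is not shown.** Quota sampling does not create confounding. Region confounds only if it is related to both exposure and outcome, and the article gives no regional data on either. Socioeconomic variables are collected, and the Reliability of Data Collection section describes certification, identical instruments and standardised interviewing. This stands: confounding can be called plausible, no more.
- **The screen works where it matters most.** A reader might infer from step 5 that the plan carries a 44% false-positive rate. It does not. That figure holds only if region is never considered, or for the unadjusted simple regressions. Where the screen often misses region, the induced correlation is small. This also stands.
- **The article is silent rather than wrong.** Listing each covariate, or specifying weights, can be left to a fuller document. A reader might infer that the plan rules out region or weights; the article does not say so. The interaction allowance even names Emirati as a factor. Since every participant is Emirati, that may be meant as emirate. But the rule for admitting covariates is stated, and so is the label, and the point rests on those two statements.
- **The counts are a poor denominator.** They cover all ages and both sexes, come from 2010 to 2020 and omit one emirate. The article never claims proportional allocation, and the quotas are approximate. This limits how exactly the disproportion can be stated, though Dubai is over-represented in every case tried.
- **Eligibility is openly stated.** It narrows the target population and is no analysis error. The national label, however, does not carry that restriction.

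**Conclusion.** The concern holds in two parts of unequal weight.

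The representativeness claim is not supported by the design. About 104 of 260 women come from one hospital and the rest from selected clinics with no probability sampling described. Women with chronic illness are excluded, and Dubai is over-sampled about 1.2- to 1.7-fold on the article's own counts. The range rests on the assumed size of the seventh emirate. The single-hospital coverage does not depend on any assumption, and no analysis can repair it.

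The covariate rule leaves the design stratum to chance: a region effect explaining 2%, 3% or 5% of outcome variance is admitted with probability 41%, 58% or 82% at 194 analysed. Region may therefore confound the associations. The stronger reading, that it does confound them, goes beyond the documents, and where the screen misses region the residual bias is likely small. The case for changing the rule is that the safeguard is almost free.

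**What to change.** 1. Enter region (or site) as a fixed covariate in all multivariable models, whatever its P-value. Region costs 2 degrees of freedom: power about 79.6% instead of 80.0%, or 2 more women analysed (196 × 1.35 = 264.6, so 265 against 260). Using site costs more, by an amount that depends on the number of sites, which the article does not give.
2. Report the descriptive profile estimates by region. This needs no further data.
3. Replace the national-representative label with multi-centre clinic-based cohort, qualify the population-based description, and state the single-hospital coverage of Abu Dhabi and the eligibility restrictions as limits. This costs nothing beyond a more modest claim.
4. Treat weighting as optional, as a sensitivity analysis of the descriptive estimates, and only if complete population margins are available. With W the population share and q the quota, the design effect Σ W²/q is 1.03 to 1.10 over the cases tried, an effective size of about 237 to 253 of 260. Weights would not repair selected-clinic or single-hospital recruitment.
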